Primary analyses will be unadjusted for covariates. A secondary analysis will adjust for baseline covariates to reduce bias associated with any chance imbalances between study arms at baseline and possibly increase efficiency (Pocock et al. 2002). We will pre-specify a potential covariate adjustment set of baseline variables and only adjust for covariates among this set that are associated with each outcome (likelihood ratio test p-value < 0.2).

Analyses will be intention-to-treat. The following households will be considered non-compliant: 1) control households that install concrete floors that cover at least one entire room inside the mother’s household; 2) households that cover at least one room’s floor with a cement finish; 3) intervention households that remove any part of the concrete floor installed as part of the trial; 4) intervention households in which a substantial portion of the concrete floor is damaged. If non-compliance exceeds 10% in either arm, we will perform a per-protocol analysis as well. We will not adjust for multiple comparisons because the number of outcomes is relatively modest, and the analysis will follow a pre-specified analysis plan.

We will compare attrition rates at each follow-up and across follow-ups between randomised arms and compare baseline characteristics of those lost to follow-up to those who complete the study. If there is evidence of systematic differences in attrition between arms and attrition exceeds 20%, we will explore whether study drop out resulted in selection bias using inverse probability of censoring weights with flexible machine-learning based estimation (Mark J. van der Laan 2011).

For STH measured in floor dust samples, the primary analysis will impute STH prevalence as 0 for floors that do not contain enough dust for nucleic acid extraction (0.1 g). The imputation assumes that floors with no dust do not harbor STH eggs. Our pilot data indicate that concrete floors in 40% of households may yield insufficient dust for nucleic acid extraction. We will conduct a secondary analysis by comparing STH outcomes in floor dust between intervention and control groups only using data from households where sufficient dust was obtained. We expect this analysis to yield a conservative estimate of intervention effectiveness because it will exclude intervention households with dust-free floors which are less likely to harbor STH eggs.

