We will explore potential effect modification by the following baseline variables: household wealth, household WASH infrastructure, presence of animals inside the household, primary play location of children <2 years, index child sex, household distance to nearest permanent water body (Pekel et al. 2016), and ordinary portland cement vs. green cement. We will also assess effect modification by monsoon vs. dry season using a data-based definition and precipitation, temperature, and humidity levels (Nguyen et al. 2024) using weather station data from the Government of Bangladesh Meteorological Department. We will test for effect modification on the relative scale by including interaction terms between these variables and treatment group indicator variables in regression models. We will estimate additive scale interactions from log-linear models using the relative excess risk due to interaction (RERI) (Knol et al. 2011). To test for effect modification, we will estimate p-values on the interaction terms for relative scale interaction in log-linear models and for additive scale interaction RERIs (Knol et al. 2011; Assmann et al. 1996).

To assess whether any post-treatment variables mediate intervention effects, we will perform causal mediation analyses (Tingley et al. 2014) for the following potential mediators: deworming or antimicrobial consumption of birth cohort or other household members in the past 6 months, and floor coverings. Interim reductions in STH could result in reduced deworming use, which in turn, further reduces STH at the final follow-up measurement. Additionally, installation of concrete may alter the type and frequency of floor coverings used, which may influence health outcomes. We will also use causal mediation analysis to assess whether health and child development outcomes are mediated through environmental vs. maternal pathways. For the environmental pathway, mediators will include contamination of the home with *E. coli* and STH. For the maternal pathway, mediators will include maternal discretionary time use; maternal bandwidth (measures of executive function, inhibition, and working memory); and maternal quality of life, stress, and depression.

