Most probable number of cefotaxime-resistant *E. coli* in household floor samples	Cefotaxime-resistant *E. coli* enumerated by IDEXX with cefotaxime supplement in household floor swabs at any follow-up measurement (6, 12, 18, 24 months)
Prevalence of extended-spectrum beta-lactamase producing *E. coli* (ESBL-E) and ESBL coding genes in household floor samples, courtyard soil, child hand rinses, drinking water, prepared food, cow feces and chicken feces	ESBL-E and ESBL coding genes in floor swabs, courtyard soil, child hand rinses, drinking water, prepared food, cow feces and chicken feces at 6 months follow-up
Mass of floor dust (g per m^2^)	Mass of dust on floors collected by sweeping a 2 m^2^ floor area next to bed where child sleeps at night (6, 12, 18, 24 months)
Relative abundance and diversity of human pathogens	Human pathogens detected in floor soil, cow feces and chicken feces samples using shotgun metagenomic sequencing each follow-up round
Relative abundance and diversity of antimicrobial resistance genes	Antimicrobial resistance genes detected in floor soil, cow feces and chicken feces samples using shotgun metagenomic sequencing each follow-up round
*Floor outcomes*	
Rate of floor sweeping and refinishing	Mean number of times floors were swept per household-day at each follow-up measurement and mean number of times floors were refinished per household-month at each follow-up measurement (6, 12, 18, 24 months)
Prevalence of holes or cracks in household floors	Proportion of household floors with holes or cracks at each follow-up measurement (6, 12, 18, 24 months)
Prevalence of impermeable household floors	Proportion of household floors in which surface water was still present after 1 minute at each follow-up measurement (6, 12, 18, 24 months)

**Table 2: T2:** Summary of variables measured in surveys

		Baseline	Birth	3 mo.	6 mo.	12 mo.	18 mo.	24 mo.
Household characteristics	Household construction materials	X			X	X	X	X
	Household census	X			X	X	X	X
	Household assets	X			X	X	X	X
	Parental education and employment	X			X			X
	WASH infrastructure & practices	X			X	X	X	X
	Animal ownership & husbandry	X			X	X	X	X
	Animal presence in the home	X			X	X	X	X
	Human and animal feces in the home	X			X	X	X	X
Perinatal outcomes	Prenatal and birth outcomes		X					
Anthropometry	Length, weight, head circumference	X	X	X	X	X	X	X
Illness symptoms	Child illness symptoms (e.g., diarrhea)	X			X	X	X	X
Flooring	Floor durability assessment	X			X	X	X	X

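### Floor dust under 0.1 g is scored STH-negative although it was not tested; because this may affect about 40% of concrete floors, the rule itself can pull the floor-dust prevalence ratio below 1

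*Protocol article*

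**What the plan says.** The Statistical analysis section sets the rule for STH by qPCR in floor dust: "the primary analysis will impute STH prevalence as 0 for floors that do not contain enough dust for nucleic acid extraction (0.1 g"). It gives the reason: "The imputation assumes that floors with no dust do not harbor STH eggs". It also gives the expected scale: "Our pilot data indicate that concrete floors in 40% of households may yield insufficient dust for nucleic acid extraction". A secondary analysis compares the arms "only using data from households where sufficient dust was obtained". The protocol expects that analysis to be conservative because "it will exclude intervention households with dust-free floors which are less likely to harbor STH eggs".

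Table 1 lists floor-dust STH as a secondary environmental outcome at 6, 12, 18 and 24 months. It lists dust mass separately: "Mass of dust on floors collected by sweeping a 2 m^2^ floor area next to bed where child sleeps at night". Dust is swept from up to 2 m² (Environmental sample collection) in a subsample of 400 households (Follow-up measurements). For the environmental pathway in the mediation analysis, "mediators will include contamination of the home with *E. coli* and STH".

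**The concern.** The rule and its justification do not cover the same floors. The trigger is less than 0.1 g; the assumption concerns floors with no dust. Over a fully swept 2 m², 0.1 g is 0.05 g per m². A floor yielding 0.09 g has dust on it that nobody assayed, so a zero there is an assumed result.

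This matters because falling short of the threshold is tied to the intervention. Concrete floors shed less dust, so the zeros fall mainly in the intervention arm. No planned analysis gives the untested samples anything but zero or exclusion. The trial could report less STH on concrete floors when part or all of that difference came from the scoring rule.

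**Working it through.** **Inputs from the protocol.** Failure share on concrete floors, fT = 0.40 (pilot; no counts are given, so it cannot be re-derived). Dust subsample 400, or about 200 per arm, since sampling is stratified by block and arm. Effect measure: prevalence ratio (PR). The protocol states no PR for this outcome, so there is none to reproduce.

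**Assumptions.** Failure share on soil floors, fC: not stated, taken as about 0, with 0.05 to 0.20 shown. Relative positivity of low-dust against sufficient-dust floors, r: not stated, range 0 to 1 shown. Control prevalence p = 20% for the error rates only.

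**1. Equal contamination everywhere (r = 1).** Observed PR = p(1 − fT) / [p(1 − fC)] = (1 − fT)/(1 − fC); p cancels.

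| fC | PR |
|---|---|
| 0 | 0.60/1.00 = 0.60 |
| 0.05 | 0.60/0.95 = 0.63 |
| 0.10 | 0.60/0.90 = 0.67 |
| 0.20 | 0.60/0.80 = 0.75 |

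With fC = 0 and fT = 0.30 or 0.50, PR is 0.70 or 0.50.

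**2. Low-dust floors cleaner (r < 1), fC = 0, same overall prevalence in both arms.** Only the positives on sufficient-dust floors are counted, so PR = 0.6/(0.6 + 0.4r).

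| r | PR |
|---|---|
| 1 | 0.60 |
| 0.5 | 0.6/0.8 = 0.75 |
| 0.25 | 0.6/0.7 = 0.86 |
| 0 | 1.00 |

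The same factor multiplies any true effect. If assayed concrete floors match control and r = 0.5, the true PR is 0.6 + 0.4 × 0.5 = 0.80 and the rule reports 0.60, which is 0.75 × 0.80.

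**3. Chance of p < 0.05 with no true difference.** Wald test on log PR, 200 per arm, one round, p = 0.20, fC = 0. SE² = (1 − p1)/(200 p1) + 0.80/(200 × 0.20), where p1 is the zero-filled intervention prevalence.

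- r = 1: p1 = 0.12; SE² = 0.0367 + 0.0200, SE = 0.238; z = 0.511/0.238 = 2.15; chance about 57%.
- r = 0.5: p1 = 0.15; SE² = 0.0283 + 0.0200, SE = 0.220; z = 0.288/0.220 = 1.31; about 26%.
- r = 0.25: p1 = 0.171; SE² = 0.0242 + 0.0200, SE = 0.210; z = 0.154/0.210 = 0.73; about 11%.

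The nominal rate is 5%. Over four rounds, with an assumed within-household correlation of 0.1 to 0.4 (design effect 1 + 3 × correlation, so 1.3 to 2.2), the chances are about 83-96%, 42-63% and 17-25%.

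**4. If the outcome is collapsed to positive at any of four rounds** (r = 1, fC = 0): with independent failures each round, PR = [1 − (1 − 0.6p)⁴]/[1 − (1 − p)⁴], which is 0.62, 0.68 or 0.81 at p = 5%, 20% or 50%. If the same floors fail every round it stays at 0.60.

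**5. Sufficient-dust analysis in the scenario of step 2.** PR = 1/(0.6 + 0.4r): 1.00 at r = 1, 1/0.8 = 1.25 at r = 0.5, 1/0.7 = 1.43 at r = 0.25. It is unbiased at r = 1 and errs against the intervention when r < 1. The two planned analyses therefore err in opposite directions for r between 0 and 1, and neither covers the middle.

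**The case against.** The outcome is STH on the floor, not STH per gram of dust, and removing soil is how the intervention is meant to work. An area that yields almost nothing when swept plausibly carries fewer eggs, so some of the fall in dust is real effect. This stands. It is why r below 1 must be shown, and why it does not follow that the rule merely counts the dust-mass outcome a second time.

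The protocol also discloses the assumption and the pilot rate and plans a sufficient-dust analysis. If assayed dust showed no difference, a reader would see it there. That limits the harm. It does not resolve the mismatch between trigger and rationale, and it leaves no analysis with intermediate values.

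Replacing the zero rule with the tested samples alone is not clearly better. That comparison conditions on a post-randomisation variable strongly affected by treatment, and multiple imputation below 0.1 g would extrapolate where no sample was ever assayed. This stands too, and argues for a range of estimates rather than a new single primary analysis.

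A reader might infer that the zero-filled variable enters the mediation analysis. The protocol does not say so: it names home contamination with STH without saying which measure, and Table 1 also has larvated ova by microscopy.

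**Conclusion.** The point holds for the secondary floor-dust STH outcome. The zero rule is wider than the assumption that supports it, and it can by itself move the PR below 1. With fT = 0.40, no true difference and almost no control failures, the PR is 0.60 to 0.86 for r from 1 down to 0.25, and reaches 1.00 only if every low-dust floor is truly negative. With equal contamination and 5-20% control failures it is 0.63-0.75. At an assumed 20% prevalence, the one-round chance of a significant result is about 57%, 26% or 11% for r = 1, 0.5 or 0.25.

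A reader might infer that the rule produces a PR of 0.60 outright. The documents do not support that: it requires low-dust floors to be as contaminated as the rest and control floors almost never to fail, and the protocol states neither. It also says only that 40% of concrete floors may fall short. Nor is the trial's primary outcome, STH in child stool, affected.

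**What to change.** In the Statistical analysis section:

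- Limit the zero rule to floors where no dust was recovered, and treat samples above zero but below 0.1 g as untested.
- Report the share of failed samples by arm and round.
- Present the result with all untested samples negative as a labelled best-case estimate. Beside it, show the sufficient-dust estimate and estimates giving untested samples non-zero positivity: for example half the assayed concrete-floor prevalence, equal to it, and the control prevalence.
- Claim a reduction in floor STH only if it holds across the plausible values.
- Do not describe the sufficient-dust analysis as conservative in advance. It conditions on a post-randomisation variable, so the direction of its bias is an expectation, not a guarantee.
- State which STH measure serves as mediator. If it is floor-dust STH, repeat that analysis without the zero-filled values.

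Dust mass is already an outcome, so no new data are needed. The cost is a few sensitivity analyses and a less favourable or less precise environmental estimate.

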### Randomisation

The trial will use household-level randomisation stratified by geographic block. This design will ensure that intervention and control groups are evenly distributed across the study area and support baseline balance of participant characteristics between arms. Using a block randomised design is also expected to increase study efficiency by accounting for strong geographic clustering of enteric infection (Arnold et al. 2024). As households are enrolled, they will be formed into geographic blocks of 10 spatially contiguous households. There will be no spatial overlap in geographic blocks. Using R statistical software, a Stanford investigator not involved in the data collection will randomly assign households within each block to control and intervention arms in a 1:1 ratio. A random subsample of 50 intervention households stratified by block will be assigned to receive a green concrete floor. Due to the nature of the intervention, it will not be possible to blind participants to a randomised study arm. Laboratory staff and data analysts will be blinded during primary and secondary outcome analyses of intervention effects.

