	Floor hygiene and maintenance	X			X	X	X	X
Child activities	Child motor skills				X	X	X	X
	Child cognitive development					X		X
	Child feeding practices				X	X	X	X
	Child play locations				X	X	X	X
Maternal outcomes	Quality of life	X		X		X		X
	Satisfaction with housing	X			X	X	X	X
	Perceived Stress Scale	X		X		X		
	Edinburgh Postnatal Depression Scale	X		X		X		
	Maternal bandwidth				X		X	
	Maternal time use			X		X		
Flooding status	Household flooding status	X			X	X	X	X
Water, sanitation, handwashing	Water storage, latrine access, child feces management, handwashing	X			X	X	X	X
Vaccination	Vaccination status of index child			X	X	X	X	X
Deworming and antimicrobials	Deworming status of household members	X			X	X	X	X
	Antimicrobial use of mother and index child	X			X	X	X	X
	Antimicrobial use in domestic animals	X			X	X	X	X
Food consumption	Animal milk consumption practices				X	X	X	
Environmental sampling	Environmental sample collection				X	X	X	X

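### Cement type is listed as a baseline effect modifier, but it is a randomised version of the intervention: its interaction term is aliased and its RERI is undefined

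*Protocol article*

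**What the plan says.** In the Protocol article, Statistical analysis, the paragraph on effect modification opens "We will explore potential effect modification by the following baseline variables". The list that follows ends with "and ordinary portland cement vs. green cement". Relative-scale modification is to be tested "by including interaction terms between these variables and treatment group indicator variables in regression models". Additive-scale interaction is to be estimated as RERI from log-linear models, and p-values are planned on both scales. No item on the list is exempted.

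The Randomisation section states: "A random subsample of 50 intervention households stratified by block will be assigned to receive a green concrete floor". The Intervention section repeats that the fly-ash mix goes to 50 households of the treatment arm, and says that control households receive no intervention.

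The Cost-effectiveness section adds that the analysis will be repeated for green floors if their cost differs from that of ordinary concrete.

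**The concern.** An effect modifier must be able to take each of its values in both arms. The question is whether the effect of the floor differs between households with and without the characteristic. Cement type does not meet this condition. It is a property of the floor that was installed, it is assigned at random within the intervention arm, and it has no value in the control arm. The stated method therefore cannot be applied to it as written.

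At stake is the health comparison of the lower-emission floor with the ordinary one. The trial randomised that subsample deliberately, and readers of a green-floor cost-effectiveness analysis would look for the comparison. If the specification stays as it is, the analyst will meet a redundant column and an undefined RERI and will have to improvise. The article relies on a pre-specified plan as part of its reason for not adjusting for multiple comparisons, so improvisation is best avoided.

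**Working it through.** **Cells.** Inputs: 800 households allocated 1:1 in blocks of 10 (Abstract), hence 80 blocks; 400 intervention households (Intervention); 50 green floors, all in that arm (Randomisation).

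| | Not green | Green |
|---|---|---|
| Control | 400 | 0 |
| Intervention | 350 | 50 |

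**Relative scale.** Let T = 1 for intervention and G = 1 for green. The planned model is log p = b0 + b1·T + b2·G + b3·T·G. For the three groups that exist:

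- control: b0
- ordinary concrete: b0 + b1
- green concrete: b0 + b1 + b2 + b3

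Three groups cannot identify four parameters. G = 1 occurs only where T = 1, so G and T·G are identical and only the sum b2 + b3 is determined. In the design as described, the matrix [1, T, G, T·G] has 4 columns and rank 3. With 80 block indicators in place of the intercept it has 83 columns and rank 82. Setting cement type to missing in controls does not help: the controls then leave the model and T is constant.

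The estimable sum is b2 + b3 = log(p green / p ordinary). This is a contrast between two floors.

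**Additive scale.** RERI = RR11 − RR10 − RR01 + 1, where RR01 is the ratio for green cement without the intervention. That cell has 0 households, so RR01, the RERI and its p-value are undefined. If software drops a column and sets RR01 to 1, the formula gives RR11 − RR10. That is the difference between the two floors' ratios against control, not an interaction.

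**Replacement model.** A three-level treatment (control, ordinary, green) with 80 block indicators has 82 columns and rank 82, so it is estimable.

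**Precision of green versus ordinary.** The article gives no figure for this contrast. From the Sample size calculation: control prevalence 20%, prevalence ratio 0.70, intraclass correlation 0.066, 15% loss, two-sided 5% error, 80% power. Assumptions made here: prevalence with ordinary concrete is 0.20 × 0.70 = 0.14, all four rounds are used, and block conditioning is ignored.

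- Evaluable households: 50 × 0.85 = 42.5, taken as 43; 350 × 0.85 = 297.5, taken as 298.
- Variance factor for four rounds: (1 + 3 × 0.066)/4 = 0.2995.
- Effective numbers: 43/0.2995 = 143.6 and 298/0.2995 = 995.0.
- Requirement: effect / standard error = 1.96 + 0.84 = 2.80.

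Log-ratio scale, which matches the planned log link, at ratio 1.62 (p = 0.2268): variance = 0.7732/(0.2268 × 143.6) + 0.86/(0.14 × 995.0) = 0.0237 + 0.0062 = 0.0299, standard error 0.173. Log 1.62 = 0.482, and 0.482/0.173 = 2.79. The detectable ratio is about 1.62.

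Difference scale with unpooled variance, at ratio 1.75 (p = 0.245): difference 0.105, standard error √(0.245 × 0.755/143.6 + 0.14 × 0.86/995.0) = 0.0375, and 0.105/0.0375 = 2.80. The detectable ratio is about 1.75. A pooled-variance test lies between, at about 1.67.

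Under the same assumptions, power (pooled-variance test) is about 21% for a true ratio of 1.25 and about 58% for 1.5.

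**The case against.** The strongest reply is that little is lost. Software would drop the redundant column, and the surviving coefficient is the log prevalence ratio of green to ordinary floors. A three-level treatment spans the same column space, so on the relative scale the change is one of labelling. This stands, and it rules out the stronger reading that the cement comparison yields no estimate at all. What does not survive is the interaction as a separate quantity, the RERI, and any description of the result as effect modification by a baseline variable.

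It is also fair that the analysis is exploratory, and that an analysis plan not shown may code the variable properly. The first point limits the importance. The second does not remove the problem, because the article positively assigns this variable to a method that cannot apply to it. Nor does the article claim equivalence of the two floors; the precision figures are a caution for reporting, not a correction of anything it states.

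A reader might also infer that a second listed modifier, "primary play location of children <2 years", is really measured after treatment, since the Table 2 row "Child play locations" is marked only at 6, 12, 18 and 24 months. The documents do not support that. The Baseline survey section records the activities of a non-index child under 3 years, the modifier is expressly called a baseline variable, and its wording is not limited to the index child. At most, the missing baseline mark in Table 2 is a discrepancy to reconcile.

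**Conclusion.** The point holds for cement type alone. As written, its treatment interaction cannot be separated from its main effect, and its RERI and p-value are undefined. Both conclusions are algebraic and rest only on green floors being confined to the intervention arm, which two sections state. The relative-scale contrast of green with ordinary concrete remains available as a randomised comparison of treatment versions.

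That contrast can detect only a ratio of roughly 1.6 to 1.75, depending on the scale of the test and on the assumed 14% prevalence, 15% loss, four rounds and correlation of 0.066. A non-significant result would say little about whether the floors perform alike. The primary analysis, the secondary outcome comparisons and the other listed modifiers are unaffected. This is a specification error worth correcting in an exploratory analysis, and no more than that.

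**What to change.** Remove cement type from the list of effect modifiers and from the RERI analysis. Add a sentence saying that cement type is a randomised version of the intervention, to be analysed with a three-level treatment (control, ordinary concrete, green concrete) and block terms. Report green versus ordinary and green versus control as prevalence ratios with confidence intervals, and state that absence of a significant difference will not be read as equivalence.

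Separately, reconcile the play-location row of Table 2 with the Baseline survey and Statistical analysis sections, by adding the baseline mark or by saying which baseline report is used.

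The cost is a wording change and one recoded variable. No new data, sample size change or change to the primary analysis is needed.
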